**Study design:**

***Location(s):*** The three HIV/AIDS treatment facilities where the beta-testing will take place are: 1) HIV Primary Care Clinic, Atlanta, GA; 2) AIDS Action Coalition, Huntsville, AL; and 3) the Borinquen Medical Center, Miami, FL.

The waiting room at the Borinquen Medical Center is not exclusively for HIV-positive patients; therefore, the video will be shown across the street in the Medical Center’s HIV case management office. The systematic observations will be conducted in the waiting room of the case management office, and patient medical data will be abstracted from Borinquen Medical Center’s EMR system.

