***Data analysis plan, including statistical methodology and planned tables and figures:***

Analysis of observational data: Patient engagement with the video during the first half of each assessment (i.e., all waiting room patients) will be analyzed qualitatively and separately for each of the six video segments (i.e., opening, three stories, and two animations). Codebooks for the content analyses will be developed after the data are received. Content analyses of the observations will look for number of patients who watch or ignore the segment and if the segment elicits any positive or negative responses. Relationships will be sought between frequency of disengagement (i.e., number of patients who ignored or exhibited a negative reaction during a segment) and characteristics of the disengaged patients (i.e., apparent age, gender, race/ethnicity). Patient engagement during the second half of each assessment (i.e., four select patients) will be analyzed the same way; however, analysis will attempt to identify within segments the scenes that are associated with patient disengagement. In addition, data from the second half of the assessments will be evaluated quantitatively for estimated duration of engagement with each segment. Patterns of disengagement across the three facilities will be sought. We will use EZ-Text qualitative software to assist with our qualitative data analysis.

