Bias is inherent in the study because the 10-month data collection timeframe is less than the 12 months required by core indicators for the outcomes being evaluated. Patient populations among the facilities are heterogeneous, so combining their medical data cannot be done reliably. Bias can occur from loss to follow-up (i.e., failure to return to the clinic) in either beta-test period. This attrition will be adjusted for analytically. Use of historical comparison will tend to exaggerate treatment effect as patients in this group benefit from amount of health care over time. Bias also can result from differences in individual medical care providers recording medical tests performed and treatment regimens prescribed and not performing medical tests at each clinic visit. Bias also can result from providers not testing all potentially infected anatomical sites for STDs. Bias may be introduced if there is a change in treatment guidelines during the 20-month data collection period.

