**1. Initial waiting room conditions**

Survey Monkey will stamp the date and time automatically. The other variables collected in this section include:

- Clinic where observations are being done
- Video version (English only/ English with Spanish Subtitles)
- Audibility (i.e. can video be heard throughout the waiting room)
- Number of monitors playing video in waiting room
- General conditions of waiting room that would impact patients’ engagement with video

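### Disengagement is defined as a count and related only to the disengaged patients, so the demographic comparison in Objective 1 has no denominator

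*Protocol*

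**What the plan says.** In the Protocol, Section III.D, Data analysis plan, the first half of each assessment (the whole waiting room) "will be analyzed qualitatively and separately for each of the six video segments". The plan counts both sides of engagement: "Content analyses of the observations will look for number of patients who watch or ignore the segment". The demographic step is narrower. It seeks relationships between the frequency of disengagement, defined as the "number of patients who ignored or exhibited a negative reaction during a segment) and characteristics of the disengaged patients (i.e., apparent age, gender, race/ethnicity". The second half of each assessment, which follows four select patients, is to be handled in the same manner, with added attention to scenes and a quantitative look at duration of engagement per segment. The paragraph also says that patterns over the three facilities will be looked for. It neither pools the facilities nor places the demographic relationship within facility.

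Objective 1 (Section II, Objectives) asks which segments engage patients better or worse among various ages, genders and race/ethnicities.

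**The concern.** The measure is not left open for a later document: the plan defines it as a number of patients. A number of disengaged patients depends on the disengagement rate in a group and on how many of that group were observed. If only the disengaged are described, the two cannot be separated, and at equal rates their demographic profile simply mirrors who was watched.

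In the select-patient half, who is watched depends partly on the observer's choice, because Appendix 2 asks for a diverse selection. The number at risk also changes by segment as patients leave, are replaced or are marked N/P.

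The findings are meant to guide refinement before national dissemination. A scene could be marked as losing a particular group when that group was only more numerous among those observed.

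**Working it through.** The plan states no rate, power or significance level for this analysis, so there is no figure to reproduce. All disengagement rates below are assumptions.

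**Inputs from the Protocol**
- Observed patients: 192 to 336 over 24 assessments (Section III.D, Bias in data collection). The sampling subsection of III.B gives 32 assessments, but three facilities times 8 is 24. The ratios below do not depend on this.
- Clinic population at least 55% African American and Hispanic/Latino (Section III.B, inclusion criteria). Using 55% as the share in the waiting room is an assumption.
- Select patients: 6 to 8 assessments per facility with four patients each (Appendix 2).

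**1. Group size, equal rates.** Expected count = N × share × rate. The ratio of counts is share/(1 − share), whatever N and the rate.
- Share 55%, N = 192, rate 20%: 192 × 0.55 × 0.20 = 21.1 against 192 × 0.45 × 0.20 = 17.3; ratio 1.22.
- Share 55%, N = 336, rate 40%: 73.9 against 60.5; ratio 1.22.
- Assumed shares of 70% and 85%: ratios 0.70/0.30 = 2.33 and 0.85/0.15 = 5.67.

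The rate ratio is 1 in every line. Dividing each count by the number observed in that group removes the artefact.

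**2. Facility.** Assume equal numbers per facility and no group difference inside any facility. The rate over all facilities is Σ(share × rate)/Σ(share) for the group, and the same with (1 − share) for the others.
- Shares 55/70/85%, rates 20/30/40%: (0.11 + 0.21 + 0.34)/2.10 = 31.4% against (0.09 + 0.09 + 0.06)/0.90 = 26.7%, a gap of 4.8 points before rounding.
- Same shares, rates 20/30/60%: 0.83/2.10 = 39.5% against 0.27/0.90 = 30.0%, a gap of 9.5 points.
- Equal rates over facilities, or equal shares: gap 0.

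A gap therefore needs both the mix and the rate to differ by site, and it arises only if the data are combined without regard to site.

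**3. What the form can support (Appendix 3).**
- All-patient half: items 2c to 2e count everyone in the room by group. Items 2a (unobstructed view) and 2b (can be observed) are single room totals. Engagement by group appears only as free text in items 2g to 2l. Group proportions cannot be formed from these fields.
- Select-patient half: the form holds clinic, demographics per patient, and reactions, duration watched and N/P per patient and segment. Group proportions can be formed. Initially selected patients number 6 × 4 = 24 to 8 × 4 = 32 per facility.

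**The case against.** Several points against the concern stand.

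- **Segments.** Analysis is by segment, and largely the same people sit through all six within one cycle. Counts therefore rank segments on nearly a common denominator. Finding weak segments, the core of the refinement work, is mostly protected.
- **Engaged patients are not ignored.** Watchers are counted, room composition is recorded, the free-text items ask whether engagement varied by group, and codebooks are to follow. This softens the point but does not remove it, because the relationship as stated still uses the disengaged only.
- **Room size.** The observed range averages 192/24 = 8 to 336/24 = 14 patients per assessment. At an assumed 30% rate that is 2.4 against 4.2 disengaged. This applies to the all-patient half only; the other half aims at four patients whatever the room.
- **Diverse selection.** It works against dominance by a majority group in the select half. It also makes counts by group depend on selection, so a denominator is still needed.

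A reader might infer that the plan pools facilities and will present site differences as demographic effects. The text does not support this. Pooling is never stated, and looking for patterns over the three facilities can mean comparing them. The remark "Patient populations among the facilities are heterogeneous" concerns the medical data. For Miami, "The systematic observations will be conducted in the waiting room of the case management office", so that setting does differ. Otherwise the form records items such as "Audibility (i.e. can video be heard throughout the waiting room") because conditions may differ, not because they are known to. Nor does the largest group always supply most of the disengaged: per 100 observed, 55 at 20% give 11, while 45 at 40% give 18.

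**Conclusion.** The concern holds in a limited form. As defined, disengagement is a count without a denominator, related only to the characteristics of the disengaged. The demographic comparison in Objective 1 then partly reflects how many of each group were observed: a ratio of 1.22 at an assumed 55% share, and 2.33 or 5.67 at assumed shares of 70% or 85%, all with equal rates.

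Because the relationship is not tied to facility, confounding by site is possible. The gaps of 4.8 and 9.5 points show what could happen under assumed mixes and rates. They are not estimates for this study. The documents do not show that the video would be edited for the wrong audience, only that the stated measure cannot rule out such a misreading.

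**What to change.** In Section III.D, Data analysis plan, change the observational paragraph as follows.

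- **Select-patient half:** define disengagement per segment as the number who ignored the segment or reacted negatively, divided by the number observed and present (not N/P), in each apparent age, gender and race/ethnicity group, with sparse categories collapsed. Show it descriptively by facility before any combined summary. The form has no box for ignoring a segment, so state which answer counts; None of it on the duration item is the nearest.
- **All-patient half:** describe counts relative to the number the observer could see (item 2b), and keep demographic remarks qualitative.

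The cost is a change of wording; the data are already collected and the instrument stays as it is. The downside is small cells: 24 to 32 initially selected patients per facility, spread over up to seven race/ethnicity categories, cannot carry a facility-stratified test such as Mantel-Haenszel. The results should be labelled descriptive only.

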***B. STUDY POPULATION***

***Description and source of study population and catchment area:***

The study population will be adult HIV-positive patients at three HIV/AIDS treatment facilities in different US jurisdictions. All adults who are HIV-positive patients in the participating HIV/AIDS treatment facilities during the study period will be included in the study. No patients will be enrolled as participants. Data gathered by the study will come from systematic observations in waiting rooms and routinely collected medical record data.

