***Sampling, including sample size and statistical power:***

The sample for the systematic observation will be a convenience sample of all patients who are present in the waiting room during the 1 day of observation at each facility. A maximum of 8 observational assessments will be done at each facility (32 total assessments). Each observational assessment will consist of systematic observation of all waiting room patients during one video cycle and systematic observation of four waiting room patients during the next video cycle. The four patients will be chosen randomly among patients who have a clear view of the video with the intent of obtaining diversity regarding age, gender, and race/ethnicity. See Appendix 2 for the observation protocol for additional details. The unit of analysis will be the individual patients. We do not expect to revise the sampling estimates for the study.

The sample for the patient medical record data will include all HIV-positive clinic patients and their records during the historical comparison period and the intervention period. Simplified sample size calculations were performed for rejecting the null hypothesis of equality in the proportions of successes for a specific outcome, assuming equal numbers of patients in each period. These calculations correspond to an analysis using Fisher’s exact test with a two-sided significance level of α = 5%.

For the primary outcome of medication adherence (achieving viral load suppression at 6 months), if the true proportions of successes for the two periods are 70% and 77% (historical comparison to intervention, 7% absolute improvement, 10% relative improvement), then sample sizes of 650 patients prescribed ART per period will be required to have 80% power to reject this null hypothesis. Allowing for an annual attrition rate of 25%, then sample sizes of 1157 patients per period will be required to have 80% power to reject this null hypothesis.

For the secondary outcome of retention in care at 3-7 months of follow-up, if the true proportions of successes for the two periods are 75% and 82% (historical comparison to intervention, 7% absolute improvement, 9% relative improvement), then sample sizes of 566 patients per period will be required to have 80% power to reject this null hypothesis. Allowing for an annual attrition rate of 25%, then sample sizes of 1008 patients per period will be required to have 80% power to reject this null hypothesis.

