The patient medical record data will be de-identified at the HIV/AIDS treatment facilities by facility staff before data are transferred onto an encrypted USB drive. No Personally Identifiable Information (PII) will be included. The patient ID number will be changed into a random project ID number using an algorithm before the data are transferred to the USB drive. The data that are transferred to the encrypted USB drive will be checked for PII before and after placing it on the USB drive. After transferring the data onto the encrypted USB drive, the USB drive will be mailed or shipped by express mail using FedEx to the data manager. This transfer of data will occur at three points during the 10 month intervention period. Pre-paid mailers will be supplied to each participating facility for each transfer. When the data manager receives the data, she will immediately transfer it to a secure laptop that is not connected to the internet (the wireless card will be removed). This laptop will be stored in a locked cabinet in her office, which is also locked when the data manager is not inside. The laptop will be password protected, and the password will be changed every 60 days. SAS and SPSS data analysis software, including any updates, will be installed on this laptop using a CD/DVD only. The data manager will merge data from the three facilities into a cross-facility file and will run consistency and error checks. The central, cross-facility database will undergo a final cleaning to ensure that all inconsistencies and queries have been resolved before the final patient medical record dataset is submitted to the CDC. The data manager will destroy the final patient medical record datasets and back-ups at the end of the project after CDC has confirmed receipt and approval of the data.

Both the data manager and the treatment facility staff responsible for de-identifying and transferring the data will be required to sign a Rules of Behavior document which is required by the CDC (See Appendix 1: Rules of Behavior document). Outside of the treatment facilities, only the data manager will have access to the data before its transfer to the CDC. Sentient will forward all FedEx tracking e-mails to the Contact Officer Representative. CDC will monitor the movement of USB drives from facilities to the data manager and from the data manager to the CDC.

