Analysis of patient medical data: For analytical purposes index visits are defined as a patient’s first HIV care clinic visit during a beta-test period (i.e., the historical comparison period or the intervention period). Patients may have index visits in both time periods. The index visit in each period will be time zero. Initiation of ART will be defined as the proportion of treatment-naïve patients (i.e., no previous record of an ART prescription) who are prescribed ART (as per the current treatment guidelines) on their index visit. Medication adherence will be defined as the proportion of patients prescribed ART who achieve viral load suppression (<50 copies/mL) at least 40 days after their index visit. Retention in HIV medical care is defined as the proportion of patients who are retained in care at 3 to 7 months of follow-up from their index visit. Partner protection will be assessed using a proxy measure—incident STDs. Incident STD is defined as the proportion of patients who do not have an incident STD as a function of time since their index visit. Incident STD is defined as a microbiologically confirmed STD diagnoses noted in patients’ electronic medical records (EMRs). Kaplan-Meier methods will be used to estimate the proportion of patients who achieve intervention outcomes. The analyses may be adjusted for patient-level covariates, such as age, race, gender, baseline viral load suppression, and baseline STD, as well as the three beta-test treatment facilities.

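### The sample size treats the two periods as independent groups although the same patients may be in both; for suppression and retention this probably makes the test conservative

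*Protocol*

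**What the plan says.** Protocol section III.B (description of the study population) takes in everyone eligible at the same three clinics: "All adults who are HIV-positive patients in the participating HIV/AIDS treatment facilities during the study period will be included in the study". The two windows adjoin: August 2015 to May 2016, then June 2016 to March 2017. Section III.D (data analysis plan) starts a new time zero for each patient in each window and states that "Patients may have index visits in both time periods".

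Section III.B (sampling and power) describes its basis as follows: "Simplified sample size calculations were performed for rejecting the null hypothesis of equality in the proportions of successes for a specific outcome". Both periods are taken to be of the same size. The section adds that "These calculations correspond to an analysis using Fisher’s exact test with a two-sided significance level of α = 5" per cent. For suppression at 70% against 77%, "sample sizes of 650 patients prescribed ART per period will be required to have 80% power". For retention at 75% against 82% the figure is 566 per period.

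For analysis, section III.D names Kaplan-Meier estimation, with optional adjustment for patient covariates and facility. It names no test, interval or variance for the contrast between periods. The protocol does not mention pairing, clustering by patient or within-patient correlation, and its paragraphs on bias and limitations do not list the overlap.

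**The concern.** Fisher's exact test compares two separate sets of people. Here the sets come from the same clinics in consecutive windows, and the protocol itself expects some patients in both. A patient who is suppressed or retained in one period is likely to be so in the next. The two period proportions then have a positive covariance, which a two-independent-samples calculation leaves out.

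What is at stake is precision and calibration: intervals that are too wide, a test that runs below its nominal level, and a sample size that does not describe the design. The size of the estimated effect is not at stake.

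**Working it through.** **Inputs from the protocol.** Suppression 70% v 77%, n = 650 per period; retention 75% v 82%, n = 566; two-sided 5%, 80% power, Fisher's exact test, equal numbers per period (all section III.B).

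**Inputs not in the protocol, so assumed.** f, the share of each period's patients who are also in the other period: 0.25 to 0.9. rho, the within-patient correlation of the binary outcome: 0.2 to 0.5. The largest correlation possible with these margins is 0.835 for suppression and 0.812 for retention, so the range is attainable.

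**Step 1: reproduce the plan's figures.** For two independent samples at 70% v 77%:

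- v1 = 0.70 × 0.30 = 0.2100; v2 = 0.77 × 0.23 = 0.1771; sum 0.3871.
- Mean proportion 0.735; 2 × 0.735 × 0.265 = 0.38955.
- n = (1.96 × √0.38955 + 0.8416 × √0.3871)² / 0.07² = 623 without continuity correction, 652 with it.
- Exact Fisher power at 650 per period: 0.8004.

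For retention: 540 uncorrected, 568 corrected, exact Fisher power 0.8001 at 566. Both stated sizes are therefore two-independent-sample sizes with no allowance for overlap.

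**Step 2: add the overlap.** With n patients per period,

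- Var(difference) = [v1 + v2 − 2·f·rho·√(v1·v2)] / n, where √(v1·v2) = 0.19285 for suppression.
- Under the null, the variance is the independent-samples value times (1 − f·rho).
- SE overstatement = √[(v1 + v2) / (v1 + v2 − 2·f·rho·√(v1·v2))].
- Actual type I error of the independent-samples z-test = 2·[1 − Φ(1.96 / √(1 − f·rho))].

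Example, f = 0.5 and rho = 0.3: the variance numerator is 0.3871 − 0.3 × 0.19285 = 0.3292. The SE ratio is √(0.3871/0.3292) = 1.08. The type I error is 2·[1 − Φ(1.96/√0.85)] = 0.034. The required n is (1.96 × √(0.38955 × 0.85) + 0.8416 × √0.3292)² / 0.07² = 530.

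**Step 3: results for suppression** (normal approximation, unadjusted difference; power at 650 per period):

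| f | rho | SE ratio | Actual type I error | Power, correct variance | Power, independent-samples test | Required n (base 623) |
|---|---|---|---|---|---|---|
| 0.25 | 0.2 | 1.03 | 0.044 | 0.836 | 0.823 | 592 |
| 0.5 | 0.3 | 1.08 | 0.034 | 0.874 | 0.836 | 530 |
| 0.5 | 0.5 | 1.15 | 0.024 | 0.911 | 0.851 | 468 |
| 0.75 | 0.3 | 1.13 | 0.026 | 0.902 | 0.847 | 483 |
| 0.75 | 0.5 | 1.26 | 0.013 | 0.952 | 0.873 | 390 |
| 0.9 | 0.5 | 1.35 | 0.008 | 0.971 | 0.888 | 343 |

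The power given up runs from 0.836 − 0.823 = 0.013 to 0.971 − 0.888 = 0.083, about 1 to 8 points. Retention behaves the same way: required n 459 at (0.5, 0.3) and 338 at (0.75, 0.5), against 540.

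**Which outcomes.** The point applies to suppression and retention, and to STD incidence, for which the protocol claims no power. It hardly touches ART initiation: a patient who is treatment-naïve at both index visits cannot have been prescribed ART in the first period.

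**The case against.** The strongest reply is that the protocol fixes no between-period test. Fisher's exact test appears only as the basis for calculations it calls simplified, and a separate analysis plan could specify a patient-clustered variance. That stands. The error follows only if the comparison is run as the sizing describes, and what is certain is the mismatch between the sizing and the analysis population.

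Second, the error is in the safe direction. That also stands, given positive correlation. A reader might infer that the overlap creates a risk of false-positive findings or leaves the study too small. Neither follows: the type I error is below 5%, the stated sizes are larger than needed, and even the independent-samples test keeps power of at least 0.82 at 650 in the table.

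Third, a reader might infer that Kaplan-Meier estimation is invalid here, or that the benefit of seeing the same patients twice is lost altogether. The documents do not support this. Each patient has one index visit per period, so each period's curve is sound; only a contrast that ignores the covariance between the curves is wrong. In the simple difference, stable differences among patients seen twice already cancel.

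Fourth, the size is uncertain. That most patients overlap is plausible for continuing clinics but is not stated. Adjusting for baseline suppression, which the protocol permits, would probably leave less correlation than the unadjusted figures assume.

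Finally, the data-handling text in section III.D says that "The patient ID number will be changed into a random project ID number using an algorithm". A reader might infer that IDs change between transfers. The text does not say so, and the variable list calls the ID unique. Stability across transfers is simply not stated.

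**Conclusion.** The point holds in a limited form. The sizing for suppression and retention assumes independent groups, while the analysis section allows the same patient in both, and nothing reconciles the two. Applied as sized, the comparison has the wrong standard error. Over the assumed ranges (f 0.25 to 0.9, rho 0.2 to 0.5) it is about 3% to 35% too large, with an actual type I error of about 0.044 to 0.008 and about 1 to 8 power points lost at 650 per period.

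The direction depends on positive within-patient correlation, and the magnitude on two quantities that the protocol does not give. The simple difference in proportions is not biased by the overlap. Severity is moderate to minor. The protocol's own limitations on historical comparison and unmeasured exposure remain, and a smaller standard error would not remove them.

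**What to change.** 1. In section III.D (data analysis plan), state that periods are compared with a variance clustered on project ID and that patients seen in only one period are kept. Examples are a logistic GEE with a period term, or a bootstrap that resamples patients for a Kaplan-Meier difference. McNemar's test alone would not do, because it drops patients seen once.
2. In section III.B (sampling and power), add that 650 and 566 ignore the overlap and are conservative if the within-patient correlation is positive. The sizes need not change.
3. As a supporting clarification in the de-identification text of section III.D, state that a patient's project ID is the same in every transfer, so that the two periods can be linked.

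The cost is a few sentences and a standard procedure in SAS, which the protocol already names. No new data are needed. The third item should be settled before the first transfer, because without a stable ID the de-identified files could not be linked centrally later.

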***Outcomes and minimum meaningful differences:***

The possible intervention outcomes during the intervention period compared to the 10 month period prior, include:

1. Increase in percent of patients who are retained in care (i.e., have clinic visit 3-7 months of follow-up)
2. Increase in percent of treatment-naïve patients receiving an ART prescription on the index visit
3. Increase in percent of patients achieving viral load suppression at 6 months (<50 RNA copies/mL plasma)
4. Decrease in incident sexually transmitted disease diagnoses among patients

The possible outcomes from the observation include the detection of certain video segments or parts of segments that are less engaging to viewers.

*Meaningful differences:*

As a practical matter, a 10% difference in patient medical outcomes is meaningful.

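### The primary adherence outcome is sized as suppression at 6 months but defined for analysis as suppression at any time from day 40 by Kaplan-Meier, which implies an ever-suppressed outcome

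*Protocol*

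**What the plan says.** All places are in the Protocol.

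- **Sampling, including sample size and statistical power (III.B)** sizes the study thus: "For the primary outcome of medication adherence (achieving viral load suppression at 6 months". The assumed success proportions are 70% (historical) and 77% (intervention), compared by Fisher's exact test at a two-sided 5% level, and "sample sizes of 650 patients prescribed ART per period will be required to have 80% power".
- **Outcomes and minimum meaningful differences (III.C)** lists the same time point: "Increase in percent of patients achieving viral load suppression at 6 months (<50 RNA copies/mL plasma".
- **Data analysis plan (III.D)** defines medication adherence as the proportion of patients prescribed ART "who achieve viral load suppression (<50 copies/mL) at least 40 days after their index visit". It then says "Kaplan-Meier methods will be used to estimate the proportion of patients who achieve intervention outcomes". It gives no end of window, no rule for which of several results counts, and no rule for a result that rises again.
- **Variables (III.C)** takes viral loads and their dates from the clinics' records, with no study testing schedule. **Bias in data collection, measurement, and analysis (III.D)** lists as a bias that tests are not done at every visit, and offers no remedy for it.

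**The concern.** Suppression at 6 months is a status at one time. Achieving suppression from day 40 onward, estimated by Kaplan-Meier, is naturally the time to a first event: once a patient has one result below 50 copies/mL, the curve cannot take the success back. Reading the curve at 6 months fixes the time point but still gives suppression at some time between day 40 and month 6.

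Two things follow. First, Hypothesis 2 concerns people already on treatment, for whom a lapse after a good result is part of what adherence means, and this outcome cannot register it. Second, each additional routine test is another chance to be scored a success. The video is also meant to raise retention and clinic visits (Hypothesis 4 and the Design section). If more visits bring more tests, the intervention period could look better with no change in adherence. The stated power also belongs to the 6-month proportion, which need not be the quantity analysed.

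**Working it through.** **1. The plan's own figure.** With 70% vs 77%, two-sided 5% and 80% power, the two-proportion formula with continuity correction gives 652 per period (623 without it). Exact Fisher power at 650 per period is 80.0%. So 650 is right for the comparison described.

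**2. What "ever suppressed" does to the rates.** The protocol gives neither the number of results per patient nor their within-patient correlation, so both are assumptions here. Take 70% and 77% as single-result rates, and let results within a patient follow a beta-binomial model with correlation ρ. With q = 1 − p:

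- two results: P(at least one suppressed) = 1 − [q² + ρq(1 − q)]
- three results: 1 − [q² + ρq(1 − q)] × [q(1 − ρ) + 2ρ]/(1 + ρ)

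Example, p = 0.70 and ρ = 0.6: two results give 1 − [0.09 + 0.6 × 0.21] = 1 − 0.216 = 78.4%. Three give 1 − 0.216 × 1.32/1.6 = 82.2%.

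| ρ | Results | Historical | Intervention | Difference (points) | Fisher power at 650 |
|---|---|---|---|---|---|
| any | 1 | 70.0% | 77.0% | 7.0 | 80.0% |
| 0.6 | 2 | 78.4% | 84.1% | 5.7 | 72.6% |
| 0.6 | 3 | 82.2% | 87.1% | 5.0 | 67.6% |
| 0.8 | 2 | 74.2% | 80.5% | 6.3 | 76.2% |
| 0.8 | 3 | 76.2% | 82.2% | 6.0 | 74.0% |
| 0.9 | 2 | 72.1% | 78.8% | 6.7 | 78% |
| 0.9 | 3 | 73.1% | 79.6% | 6.5 | 77% |

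**3. More testing with no change in adherence.** Set the single-result rate to 70% in both periods, with two results per patient historically. Two cases for the intervention period:

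- *Modest:* tests rise in line with the planned retention gain, 82/75 = 1.093, about 9%. Mean tests go from 2.0 to about 2.19, so 18.7% of patients have a third.
- *Extreme:* every patient goes from two tests to three, a 50% rise.

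| ρ | Rejection at 650, equal testing | Modest: shift; rejection at 650 | Extreme: shift; rejection at 650 |
|---|---|---|---|
| 0.6 | 4.3% | 0.7 points; 5.3% | 3.8 points; 37.7% |
| 0.8 | 4.3% | 0.4 points; 4.6% | 2.0 points; 12.0% |
| 0.9 | 4.3% | 0.2 points; 4.4% | 1.0 point; 6.2% |

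At the attrition-inflated 1157 per period, rejection is 4.6-6.3% in the modest case and about 8-61% in the extreme one.

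**4. Masked rebound.** Assume 5-10% of suppressed patients rebound by 6 months. The hidden share is 0.05 × 70 = 3.5 to 0.10 × 70 = 7.0 points historically, and 0.05 × 77 = 3.85 to 0.10 × 77 = 7.7 points under the video. Both periods are affected, so the difference between them moves only by 3.85 − 3.5 = 0.35 to 7.7 − 7.0 = 0.7 points.

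**The case against.** The protocol nowhere says that any one suppressed result makes a patient adherent. Forty days may simply be the earliest usable result, with 6 months as the assessment time. The Kaplan-Meier sentence covers all outcomes, including ART prescription at the index visit, which has no follow-up time, so it is weak evidence of a deliberate first-event rule. The choice among several routine results is often left to a statistical analysis plan, which is not at hand. The sample size section also speaks of achieving suppression. If 70% and 77% were meant as cumulative proportions by 6 months, the power loss in the working disappears. Kaplan-Meier is also a natural way to deliver the promised analytic adjustment for attrition. Finally, the study calls itself developmental and says it cannot show conclusively that the video caused any change.

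Most of this limits the size of the point. A reader might infer that extra testing will seriously inflate false positives; the documents do not support that, since the large figures need half as many tests again in every patient. A reader might also set the 3.5-7 points of hidden rebound against the planned 7-point effect, but that compares a level with a difference between periods.

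What the objection does not remove is the conflict itself. Two sections fix 6 months, while the section defining the analysis gives an open-ended window and an estimator that ignores everything after the first success. The limitations do not mention this.

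**Conclusion.** The point holds as a conflict over the primary outcome. The protocol sizes and lists suppression at 6 months, but defines for analysis an open-ended outcome from day 40 whose wording, combined with Kaplan-Meier, implies ever suppressed. That implication is an inference. If it is followed, loss of later rebound and dependence on testing frequency hold at any correlation short of perfect agreement between results.

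The numerical cost is moderate and uncertain. On the assumption that 70% and 77% are single-result rates, with two results per patient and correlation 0.6-0.9, power at 650 falls from 80% to about 73-78%. Type I error is hardly affected under a 9% rise in tests, and reaches 6-38% at 650 only under the extreme shift. Masked rebound moves the contrast by about 0.35-0.7 points under an assumed 5-10% rebound. The figure of 650 is not wrong. The reason to act is that the primary outcome should have one definition before the data are analysed.

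**What to change.** In the Data analysis plan (III.D), define the primary adherence outcome as suppressed yes or no on one viral load per patient per period: the result nearest to 6 months, or the last, within one fixed window around 6 months that is the same in both periods. Compare the proportions as sized in III.B, and use the same definition in all three sections.

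State how patients with no result in the window are handled, because having a result depends on retention, which the video targets. One option is to count them as not suppressed in the primary analysis, with tested patients only as a sensitivity analysis. Separate those who did not return from those whose index visit came too late: in a 10-month period, an index visit after the first 4 months (10 − 6) cannot reach 6 months. Apply the same rule to both periods.

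Report by period the number of viral loads per patient and the proportion without a result. Keep Kaplan-Meier time to first suppression as a secondary description.

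The cost is wording only, since every viral load and its date is already extracted. The downside is a somewhat lower suppression rate and a visible group with no result.
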